### 8.3 Populations for analyses

For purposes of analysis, the following populations will be defined as per **Table 6**.

**Table 6:** Population for analyses

| Population                             | Description                                                                                                                                                                                         |
|----------------------------------------|-----------------------------------------------------------------------------------------------------------------------------------------------------------------------------------------------------|
| Enrolled                               | All participants who sign the informed consent                                                                                                                                                      |
| Evaluable/Per Protocol Population (PP) | All participants who fully complied with the protocol and for whom index test results and reference test results are available for all tests.                                                       |
| Partially Compliant Population (PCP)   | All participants who complied partially with the protocol, i.e. those for whom index test results and reference test results are available but not in a complete form (e.g. missing one RDT result) |

### 8.4 Statistical analysis plan

The statistical analysis plan (SAP) will be developed and finalized before the start of enrolment and will describe the analysis strategy in detail. This section is a summary of the planned statistical analyses of the primary and secondary endpoints.

#### 8.4.1 Analysis of primary and secondary outcomes

Estimates of sensitivity, specificity, positive and negative predictive values, together with 95% confidence intervals based on Wilson's method, will be obtained based on the definitions reported in Table 7. The estimates will be obtained for each RDT separately, using either the composite reference standard or the WHO PQed HCV RDT (SD Bioline) as reference standard for the outcomes 1.1 and 2.1 respectively. Outcomes 1.1 and 2.1 will be evaluated on the PP population.

**Table 7** outlines the classification of sample results for calculation of sensitivity, specificity, PPV and NPV.

**Table 7:** Definition of test results and classification metrics

| RDT result | Composite reference standard outcome |                       |                       |         |
|------------|--------------------------------------|-----------------------|-----------------------|---------|
|            |                                      | HCV antibody positive | HCV antibody negative | Total   |
|            | HCV antibodies detected              | a                     | b                     | a+b     |
|            | HCV antibodies not detected          | c                     | d                     | c+d     |
|            | Total                                | a+c                   | b+d                   | a+b+c+d |

Definitions and calculation:

a = True Positives, b = False Positives

c = False Negatives, d = True Negatives

Sensitivity =  $a / (a + c)$

Specificity =  $d / (b + d)$

Positive Predictive value =  $a / (a + b)$

Negative Predictive value =  $d / (c + d)$

Point estimates (with 95% CI) of sensitivity, specificity, PPV and NPV will be derived separately for each site, as well as for the pooled data for all sites. In order to assess whether there is an association between the results and the clinical site from where the samples were collected, the estimates of sensitivity and specificity for each individual site will be compared with each other by use of a Pearson's chi-squared test, at a significance level of 5%, adjusted by Bonferroni correction for the total number of tests performed. A random effect model will be used if it is believed that a high site-effect is present: this will be assessed by the evaluation of heterogeneity using Cochran's Q (with a significance level set at 0.1) and the  $I^2$  statistics (with a value  $>0.5$ ).

Table 8 outlines the combinations of the reference method results and the corresponding composite reference standard outcomes. All EIA and LIA result are interpreted according to the manufacturers IFU (pos, neg, indet). See section 6.6.2 for a further explanation of the composite reference standard.

**Table 8:** Reference method results and corresponding composite reference standard outcomes

|                          |      | Composite reference standard outcome |     |     |                       |     |     |                 |     |       |       |       |       |
|--------------------------|------|--------------------------------------|-----|-----|-----------------------|-----|-----|-----------------|-----|-------|-------|-------|-------|
|                          |      | HCV antibody positive                |     |     | HCV antibody negative |     |     | Sample excluded |     |       |       |       |       |
| Reference method results | EIA1 | Pos                                  | Pos | Neg | Neg                   | Neg | Pos | Pos             | Neg | Pos   | Pos   | Neg   | Neg   |
|                          | EIA2 | Pos                                  | Neg | Pos | Neg                   | Pos | Neg | Pos             | Neg | Pos   | Neg   | Pos   | Neg   |
|                          | LIA  | Pos                                  | Pos | Pos | Neg                   | Neg | Neg | Neg             | Pos | Indet | Indet | Indet | Indet |

Additional subgroup analyses will be performed for different combinations of reference method outcomes, further detail will be provided in the statistical analysis plan.

The details on the analysis of outcome 2.2 will be described in the study SAP.

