### 1.1 Study rationale

FIND has previously conducted an extensive evaluation study of 13 HCV RDTs in reference laboratories on archived EDTA plasma samples from LMICs, with the aim to identify well-performing test that could meet WHO PQ requirements (FIND “Evaluation study of HCV RDTs”, no. 8162-2/1 [4]). A total of 1’800 archived EDTA plasma samples were analysed (800 HCV antibody +ve, 1’000 HCV antibody-ve), originating largely from LMICs (Nigeria, Georgia, Cambodia) and to a small percentage from a high income country (HIC; Belgium 6%). Half of all samples were from HIV co-infected patients (HCV+ve and HCV-ve) to determine performance in samples from patients with this frequently found co-infection. Preliminary results of this study showed that all RDTs met WHO PQ performance requirements in samples from patients not co-infected with HIV (98% sensitivity and 97% specificity [5]). In samples from HIV co-infected patients, however, performance was highly variable, with several tests showing over 10% reduced sensitivity for HCV antibodies in the presence of HIV infection (preliminary, unpublished results).

Three of the 13 RDTs from this initial study had a comparatively high performance in the HCV-mono and HCV/HIV co-infected populations, leading to an acceptable overall sensitivity and specificity for further evaluation: Beijing Wantai HCV-Ab Rapid Test (“Wantai”) (sens/spec 97.1%/97.5%); Premier Medical Corporation First Response HCV Card Test (“PMC”) (sens/spec 95.9%/99.5%); Access Bio CareStart HCV Antibody Test (“AccessBio”) (sens/spec 96.1%/97.8%).

The current study aims to conduct a clinical evaluation of these three tests on fresh whole blood, EDTA plasma and serum samples in primary healthcare settings to evaluate performance as per WHO PQ requirements [6]. The Abbott SD Bioline HCV test will be used as the comparator in the

primary healthcare setting, to compare the performance of the study RDTs to an RDT that is pre-qualified by the WHO and to enable direct comparison of RDT performance in whole blood.

The manufacturers of the three study RDTs wish to seek WHO PQ approval, have easy-to-perform tests (two steps) and are offering their current HCV RDT at low prices, making them good candidates for procurement in LMICs. The data generated during this study can be used to seek WHO pre-qualification and/or CE-marking.

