| 1.1 To determine the performance of each study RDT in fingerstick whole blood, EDTA plasma and serum in field settings, using a combination of two enzyme immunoassays (EIAs) and a line immunoassay (LIA) as composite reference standard. | 1.1 Point estimates of sensitivity, specificity, positive and negative predicative values (with 95% confidence intervals) and Cohen's Kappa Coefficient ( $\kappa$ ) of inter-rater agreement for each RDT, using a combination of two EIAs and a LIA as composite reference standard for the detection of anti-HCV antibodies in fingerstick whole blood, EDTA plasma and serum. |
| Secondary                                                                                                                                                                                                                                   |                                                                                                                                                                                                                                                                                                                                                                                   |
| 2.1 To determine the performance of each study RDT in fingerstick whole blood, EDTA plasma and serum in field settings, using an RDT already pre-qualified by WHO ("WHO PQed RDT") as reference standard.                                   | 2.1 Point estimates of sensitivity, specificity, positive and negative predicative values (with 95% confidence intervals) and Cohen's Kappa Coefficient ( $\kappa$ ) of inter-rater agreement for each RDT, using the WHO-PQed RDT as reference standard for the detection of anti-HCV antibodies in fingerstick whole blood, EDTA plasma and serum.                              |
| 2.2 To evaluate the operational characteristics of study RDTs.                                                                                                                                                                              | 2.2 Operational characteristics and usability of study RDTs:
- Rate of invalid test results /errors:
Percentage of invalid test results/errors by RDT, site and error type
- Technical appraisal rating on kit instructions, labelling and test conduct, on a Likert scale                                                                                               |

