## **3.2 Scientific rationale for study design**

Both study sites are located in resource-limited settings, which is the intended use setting for HCV RDTs to be pre-qualified by the WHO [3]. RDT testing will be performed by intended users of the tests, i.e. primary healthcare workers who routinely perform blood sampling procedures on patients, but are not experienced in performing sophisticated diagnostic laboratory testing.

Matched fingerstick whole blood, EDTA plasma and serum sample will be assessed to evaluate the performance in all sample types claimed by the RDT manufacturers. Performance of RDTs in these sample types will be compared to a composite reference standard as well as to an HCV RDT already pre-qualified by WHO (SD Bioline).

The use of a composite reference standard designed of two EIAs and one LIA, allows accurate characterisation of HCV antibody status (see section 6. Study Procedure for further detail). This method is also used by WHO PQ for sample characterisation during independent laboratory evaluations of RDTs [17]. Using a WHO-PQed HCV RDT (SD Bioline) will allow direct performance comparison in all sample types in the intended use setting.

Assessment of HCV viral load will provide additional information on the status of the infection of the patient, i.e. active or resolved. This information will be used to support the interpretation of discordant results, as some RDTs can have lower sensitivity in patients with resolved HCV infection [18].

Genotyping of HCV positive samples will allow to assess RDT performance in relation to different HCV genotypes. Study sites were chosen to ensure genotype diversity; the most prevalent genotypes in Georgia and Cambodia are 1b, 2, 3 and 1b, 6, respectively [11-13].

Testing study participants for HIV will provide important additional information, as some RDTs have shown lower performance in patients co-infected with HIV during the previous FIND HCV RDT study [4]. Furthermore, it is known that immunocompromised patients may have lower HCV antibody titres [19, 20], potentially impacting RDT performance.

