## 8 Statistical considerations

### 8.1 Statistical hypotheses

No statistical hypotheses will be tested in this study.

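### Outcome 2.1 reports agreement with SD Bioline as if it were accuracy, and the protocol specifies no contrast between a study RDT and SD Bioline

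*Protocol*

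**What the plan says.** - **Secondary outcome.** Table 2 in Section 2 defines endpoint 2.1 as sensitivity, specificity, PPV, NPV and Cohen's kappa, "using the WHO-PQed RDT as reference standard for the detection of anti-HCV antibodies". Section 8.4.1 repeats this, "using either the composite reference standard or the WHO PQed HCV RDT (SD Bioline) as reference standard for the outcomes 1.1 and 2.1 respectively".
- **Why SD Bioline is there.** Section 1.1 calls it the comparator and says it is used "to enable direct comparison of RDT performance in whole blood". Section 3.2 says: "Using a WHO-PQed HCV RDT (SD Bioline) will allow direct performance comparison in all sample types in the intended use setting".
- **What is estimated.** Objective 1.1, which uses the EIA/LIA composite, reads "To determine the performance of each study RDT in fingerstick whole blood, EDTA plasma and serum in field settings". Endpoint 1.1 and Section 8.4.1 drop the word study: "The estimates will be obtained for each RDT separately", "together with 95% confidence intervals based on Wilson's method".
- **What is contrasted.** The only between-group comparison in Section 8.4.1 is between sites. Section 8.1 states: "No statistical hypotheses will be tested in this study".
- **Discordant pairs.** Under Section 6.6.3, discordances between a study RDT and SD Bioline are retested in plasma and serum only and reported separately. The section does not say that the composite settles which test was right.

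**The concern.** Sensitivity and specificity are meaningful only against something treated as the truth. Table 7, the only 2x2 definition in the protocol, labels its cells true and false under the composite reference outcome. Outcome 2.1 carries the same labels over to a comparison with another rapid test. SD Bioline's errors are then charged to the study RDT wherever the two disagree, and hidden wherever they err together.

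The protocol gives no reason to treat SD Bioline as error-free. Section 1.1 reports that several RDTs lost more than 10% sensitivity with HIV co-infection, and Section 3.2 notes lower sensitivity of some RDTs in resolved infection. Neither section says whether SD Bioline is affected.

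The results are meant for stakeholders and for manufacturers' prequalification or CE-marking files. A figure called sensitivity or specificity may be set beside the 98%/97% requirement in Section 1.1 although it does not measure the same thing. Nor can agreement show which test was right in a discordant pair, so outcome 2.1 does not deliver the comparison for which SD Bioline was included.

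**Working it through.** **Plan's own figures.** Table 4 reproduces with n = (1.960 + 0.842)² × p(1 − p) / 0.05². This gives 283 at p = 0.90 and 150 at p = 0.95, so the sample size is not in question here.

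**Inputs.** P = 440 antibody-positive and N = 1,100 antibody-negative participants (Table 4). SD Bioline's accuracy is not stated and is varied. The study RDT is assumed to be truly 98% sensitive and 99% specific.

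**Formulas**, for errors independent given true status. Study RDT: sensitivity Se, specificity Sp. SD Bioline: Se_r, Sp_r.

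- Apparent sensitivity = [P·Se·Se_r + N(1 − Sp)(1 − Sp_r)] / [P·Se_r + N(1 − Sp_r)]
- Apparent specificity = [N·Sp·Sp_r + P(1 − Se)(1 − Se_r)] / [N·Sp_r + P(1 − Se_r)]

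| SD Bioline assumed | Apparent sensitivity (true 98%) | Apparent specificity (true 99%) |
|---|---|---|
| 98%/99% | 422.69/442.2 = 95.6% | 1078.29/1097.8 = 98.2% |
| 95%/99% | 409.75/429 = 95.5% | 1078.55/1111 = 97.1% |
| 90%/99% | 388.19/407 = 95.4% | 1078.99/1133 = 95.2% |

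The loss in apparent specificity is 0.8, 1.9 and 3.8 points and comes from SD Bioline's misses (8.8, 22 and 44 samples). The loss in apparent sensitivity comes mostly from SD Bioline's 1,100 × 0.01 = 11 false positives.

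**A perfect study RDT.** Take the evaluable 400/1,000 and an SD Bioline exactly at 98%/97%. Apparent sensitivity is 392/(392 + 30) = 92.9% and apparent specificity 970/(970 + 8) = 99.2%, although the study RDT makes no error.

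**Correlated errors.** Take both tests at the planned whole-blood 90%/90%, with 400/1,000. SD Bioline is then positive in 360 + 100 = 460 samples and negative in 40 + 900 = 940.

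| Error correlation | Apparent sensitivity (true 90%) | Apparent specificity (true 90%) |
|---|---|---|
| 0 | 334/460 = 72.6% | 814/940 = 86.6% |
| 0.5 | 397/460 = 86.3% | 877/940 = 93.3% |
| 1 (identical errors) | 460/460 = 100% | 940/940 = 100% |

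At a correlation of 0.5 sensitivity is still understated while specificity is already overstated. The direction of the bias is therefore not known in advance.

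**Would the planned sample support a paired contrast?** With discordance ψ between the two tests and a small true difference, the 95% half-width is about 1.96·√(ψ/n). For ψ from 5% to 18% this is ±2.2 to ±4.2 points for sensitivity (n = 400) and ±1.4 to ±2.6 points for specificity (n = 1,000). The range of ψ is assumed. Its upper end, 2 × 0.9 × 0.1 = 18%, corresponds to two tests at 90% with independent errors.

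**The case against.** The strongest reply is that outcome 2.1 answers objective 2.1 as written. Each figure names its reference, kappa is already planned, and a relabelled percent agreement has the same formula and value. This is an estimation study with no hypotheses, and interval methods belong in the SAP. Reactive samples also go to HCV PCR, and viral load supports the reading of discordant results. All of this is true, and it is why the matter is secondary. It does not turn agreement into accuracy, and it does not supply the comparison that Sections 1.1 and 3.2 give as the reason for running SD Bioline.

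A reader might also infer four stronger claims, which the documents do not support:

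- *The plan never scores SD Bioline against the composite.* Objective 1.1 is confined to study RDTs, but endpoint 1.1 and Section 8.4.1 refer to each RDT, which could include it. Endpoint 2.1 uses the same wording where SD Bioline is the reference, so the phrase settles nothing. The text is ambiguous.
- *The protocol promises a comparison against the composite.* It says only that SD Bioline enables or allows direct comparison. Using the composite as the yardstick is the sound way to do it, not a stated commitment.
- *A study RDT better than SD Bioline will be reported as worse than it.* Outcome 2.1 gives no accuracy figure for SD Bioline to be worse than, and outcome 1.1 reports the study RDT correctly.
- *The bias is large and always downward.* Sensitivities of 90% or 95% for SD Bioline lie below the 98% that Section 1.1 cites for prequalification. At 98%/99% the loss in apparent specificity is 0.8 points. The tests all detect the same antibodies, so independent errors may not be realistic.

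**Conclusion.** The point holds for secondary outcome 2.1 and should be corrected. The quantities labelled sensitivity, specificity, PPV and NPV there measure agreement with an imperfect rapid test. No contrast between a study RDT and SD Bioline is specified, and it is unclear whether SD Bioline itself is assessed against the composite. An SAP not shown here could add a paired analysis, but it would not change an endpoint that the protocol defines.

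The size cannot be fixed from the documents. Under the assumptions above (study RDT 98%/99%, independent errors), specificity is understated by 0.8 to 3.8 points and sensitivity by about 2.4 to 2.6 points. With correlated errors the bias shrinks, and with strong enough correlation it reverses. The primary outcome and Table 4 are not affected.

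**What to change.** 1. State in the objectives and in Section 8.4.1 that SD Bioline is also evaluated against the composite reference, in each specimen type and with the same 2x2 tables as the study RDTs.
2. For each study RDT and specimen type, report the paired difference in sensitivity and in specificity versus SD Bioline, with the discordant counts and a 95% confidence interval for paired proportions (Newcombe or Tango, for example). Present these as estimates without tests, consistent with Section 8.1.
3. Keep the planned cross-tabulation and kappa for 2.1, but label the results positive and negative percent agreement and drop PPV and NPV there.

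The cost is a wording change to endpoint 2.1 and some extra analysis. All four RDTs are already run on the three specimen types from every participant, and the composite is already planned on every plasma sample, so no further samples or tests are needed. Step 3 alone changes no number; steps 1 and 2 provide the comparison.

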| Secondary objective(s)         | 2.1 To determine the performance of each study RDT in fingerstick whole blood, EDTA plasma and serum in field settings, using an RDT already pre-qualified by WHO ("WHO PQed RDT") as reference standard.
2.2 To evaluate the operational characteristics of study RDTs.                                                                                                                                                                                                                                                                                                                                                                                                   |
| Primary endpoints (outcomes)   | 1.1 Point estimates of sensitivity, specificity, positive and negative predicative values (with 95% confidence intervals) and Cohen's Kappa Coefficient ( $\kappa$ ) of inter-rater agreement for each RDT, using a combination of two EIAs and an LIA as a composite reference standard for the detection of anti-HCV antibodies in fingerstick whole blood, EDTA plasma and serum.                                                                                                                                                                                                                                                                                          |
| Secondary endpoints (outcomes) | 2.1 Point estimates of sensitivity, specificity, positive and negative predicative values (with 95% confidence intervals) and Cohen's Kappa Coefficient ( $\kappa$ ) of inter-rater agreement for each RDT, using the WHO-PQ RDT as reference standard for the detection of anti-HCV antibodies in fingerstick whole blood, EDTA plasma and serum.
2.2 Operational characteristics and usability of study RDTs:
- Rate of invalid test results /errors: Percentage of invalid test results/errors by RDT, site and error type.
- Technical appraisal rating on kit instructions, labelling and test conduct, on a Likert scale.                                      |

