### 3 Study design

#### 3.1 General design

This is a prospective multicentre diagnostic accuracy study. The study will be conducted at primary healthcare facilities for participant recruitment and RDT testing, and at diagnostic reference laboratories for confirmatory and reference testing (see **Error! Reference source not found.**).

**Figure 1:** Overview of the general study design

[figure not shown]

\* HCV Reference testing: Enzyme Immunoassays (EIA) Diasorin Murex Anti-HCV v4.0 and Fujirebio INNOTEST HCV Ab IV; Line Immunoassay (LIA): Fujirebio INNO-LIA HCV

In Georgia, the study will be conducted at two primary healthcare facilities. One site offers opioid substitution therapy (OST) and is seeing a population with high HCV prevalence (approximately 40%). The other site is a hepatitis/HIV screening facility for the general population with a lower HCV prevalence of approximately 5%. The latter facility was chosen for the necessary number of

negative samples to be collected. The reference laboratory is the Lugar Centre, which acts as the confirmatory laboratory for both sites under the standard of care.

In Cambodia the study will be conducted at the Sihanouk Hospital Centre of Hope where the general population attends for HIV/HCV screening as well as other medical issues. The reference laboratory is the hospital's diagnostic routine laboratory. HCV viral load and HCV genotyping will be outsourced to the Institut Pasteur du Cambodge in Phnom Penh via service contract, as the Sihanouk Hospital Centre of Hope has no capacities to perform these tests (collectively referred to as "reference laboratory" in this protocol).

Participants will be enrolled sequentially as they present at the primary healthcare facilities. Any individual attending the healthcare facilities will be given the opportunity to participate in the study, regardless of the reason for the visit. At the OST site in Georgia and the outpatient clinic in Cambodia, patients with known HCV-positive serology status will be contacted and invited to participate in the study. Participants will be pre-screened for eligibility and eligible participants who wish to participate in the study will undergo the consent procedure (see section 9.3. Informed consent process) prior to the collection of demographic and clinical information, and samples for study.

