|-------------------------|-------------|-----------------------|-------|--------|-------------------------------------|-----------------------------------|----------------------------------|
| Fingerstick whole blood | Sensitivity | 90%                   | 0.8   | 0.05   | 283                                 | 400                               | 440                       |
|                         | Specificity | 90%                   | 0.8   | 0.05   | 283                                 | 1'000                             | 1'100                     |
| EDTA plasma             | Sensitivity | 95%                   | 0.8   | 0.05   | 150                                 | 400                               | 440                       |
|                         | Specificity | 95%                   | 0.8   | 0.05   | 150                                 | 1'000                             | 1'100                     |
| Serum                   | Sensitivity | 95%                   | 0.8   | 0.05   | 150                                 | 400                               | 440                       |
|                         | Specificity | 95%                   | 0.8   | 0.05   | 150                                 | 1'000                             | 1'100                     |

Each participant will provide samples for all sample types (see also Figure 2), resulting in a total of 1'540 matched fingerstick whole blood, EDTA plasma and serum sample sets.

Enrolment targets per country and site are listed in **Table 5**. Targets take into consideration local HCV prevalence and estimated number of patients to be enrolled per day

**Table 5** Enrolment targets per country and site

|                             | Approximate HCV prevalence           | Estimated number of patients recruited per day | HCV antibody positive participants | HCV antibody/RNA negative participants | Total                    |                 |
|-----------------------------|--------------------------------------|------------------------------------------------|------------------------------------|----------------------------------------|--------------------------|-----------------|
| Georgia OST site            | 40% + patients with known HCV status | 25                                             | 310                                | 140                                    | 450 per site             | 770 per country |

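### PPV and NPV in primary endpoint 1.1 come from raw counts, so at the OST and SHCH sites and in the pooled data they reflect the enrolment quotas, not the clinics

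*Protocol*

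**What the plan says.** The primary objective (Protocol section 2, Table 2) is "To determine the performance of each study RDT in fingerstick whole blood, EDTA plasma and serum in field settings". The synopsis words its endpoint 1.1 as "Point estimates of sensitivity, specificity, positive and negative predicative values (with 95% confidence intervals) and Cohen's Kappa Coefficient" for each test, against the composite reference standard.

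Section 8.4.1 fixes the estimators. Under Table 7, PPV is the number of true positives divided by all RDT-positive samples in the study. NPV is the number of true negatives divided by all RDT-negative samples. Both are reported "together with 95% confidence intervals based on Wilson's method". The section adds that "PPV and NPV will be derived separately for each site, as well as for the pooled data for all sites". It mentions no weighting or adjustment for prevalence. The same formulas serve secondary outcome 2.1.

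The mix of positives and negatives comes from section 8.2. The draft WHO TSS-7 minimums of 400 and 1,000 are raised by 10% to 440 and 1,100 and split across sites in Table 5. Section 3.1 states that at the OST site and the Cambodian outpatient clinic "patients with known HCV-positive serology status will be contacted and invited to participate in the study", and Table 5 accordingly lists the OST prevalence as "40% + patients with known HCV status". Section 3.4.1 adds that at both sites, once the target for negatives is full, only people known to be positive are enrolled. Section 4.3.2 treats this as a risk to unbiased reading of the tests. No section discusses its effect on predictive values.

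**The concern.** A raw-count PPV estimates a clinic's PPV only if the ratio of positives to negatives in the sample arises from that clinic's patients. At OST and SHCH it arises from targets. If a target changed, the PPV and NPV would change with it, although the test had not.

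The synopsis says the results will inform national and international stakeholders about performance in the field. PPV is the figure a screening programme would use to judge how many reactive results confirmatory testing will overturn. If it is inflated by enrichment, the test looks better in a low-prevalence clinic than it would be. NPV errs the other way: at the enriched OST site it would look worse than it is.

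**Working it through.** **1. The plan's own figures.** Section 8.2 gives 80% power and a margin of 0.05. With n = (1.960 + 0.842)² × p(1 − p) / 0.05²:
- p = 0.90: 7.849 × 0.09 / 0.0025 = 282.6, so 283.
- p = 0.95: 7.849 × 0.0475 / 0.0025 = 149.1, so 150.

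Both match Table 4. Also 400 × 1.1 = 440 and 1,000 × 1.1 = 1,100. The site targets sum correctly: 310 + 20 + 110 = 440, 140 + 300 + 660 = 1,100, total 1,540. The sample size stands.

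**2. Share of positives, by target and by stated prevalence** (Table 5; sections 3.1 and 3.4.1).

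| | Target | Stated prevalence |
|---|---|---|
| OST | 310/450 = 68.9% | about 40% |
| NCDC | 20/320 = 6.25% | about 5% |
| SHCH | 110/770 = 14.3% | 5% |
| Pooled | 440/1,540 = 28.6% | (450 × 0.40 + 320 × 0.05 + 770 × 0.05)/1,540 = 234.5/1,540 = 15.2% |

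The pooled comparator keeps the same site totals, so it isolates the effect of enrichment.

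**3. Formulas.** For prevalence π, PPV = Se·π / [Se·π + (1 − Sp)(1 − π)] and NPV = Sp(1 − π) / [Sp(1 − π) + (1 − Se)π]. At the target mix these equal the Table 7 ratios on expected counts.

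**4. At Se = Sp = 95%** (the plasma and serum assumption in section 8.2):
- SHCH PPV: 104.5 / (104.5 + 33) = 76.0%. At 5%: 0.0475 / (0.0475 + 0.0475) = 50.0%.
- OST NPV: 133 / (133 + 15.5) = 89.6%. At 40%: 0.57 / (0.57 + 0.02) = 96.6%.
- Pooled PPV: 418 / (418 + 55) = 88.4%. At 15.2%: 77.3%.
- NCDC PPV: 19 / (19 + 15) = 55.9%. At 5%: 50.0%.

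**5. Other accuracy assumptions** (raw count, then stated prevalence). The first is the whole-blood planning value. The second is the earlier study's average, given in the synopsis.

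| | Se = Sp = 90% | Se 96.3%, Sp 98.3% |
|---|---|---|
| SHCH PPV | 60.0%, 32.1% | 90.4%, 74.9% |
| OST NPV | 80.3%, 93.1% | 92.3%, 97.6% |
| Pooled PPV | 78.3%, 61.8% | 95.8%, 91.1% |
| NCDC PPV | 37.5%, 32.1% | 79.1%, 74.9% |

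**6. The planned intervals.** At 95%/95% the Wilson interval runs from about 68% to 82% for SHCH PPV and from about 85% to 91% for pooled PPV. Neither contains its comparator (50.0% and 77.3%). A larger sample would only narrow them around the quota-driven value.

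**7. Kappa.** Section 8.4.1 gives no formula. Standard kappa at 95%/95% would be 0.82 against 0.63 at SHCH, 0.88 against 0.82 pooled, and almost unchanged at OST (0.89 against 0.90).

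**The case against.** The strongest reply is that nothing in the study is decided on PPV, NPV or kappa. Section 8.1 tests no hypotheses. Section 8.4.2 expresses efficacy as sensitivity and specificity, and the WHO requirements quoted in section 1.1, the sample size and the between-site comparisons use only those two. A reader can also recover predictive values from the reported sensitivity and specificity. All of this stands and limits the seriousness. It does not make the stated estimator suitable for an endpoint listed as primary under a field-performance objective.

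Three stronger readings are tempting, and the documents do not support them.

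- A reader might set the pooled PPV of 88.4% against the 50.0% that holds at 5% prevalence. The pool includes a clinic with a prevalence of about 40%, so most of that gap comes from combining unlike clinics. The like-for-like comparator is 77.3%, and section 8.4.1 also reports each site.
- A reader might infer that every general-population site is distorted. Section 3.1 invites known positives only at OST and SHCH, and the NCDC target of 6.25% is close to its stated 5%. PPV there moves by about 4 to 6 points under the assumptions above.
- A reader might infer that sensitivity and specificity are compromised. They do not depend on the ratio of positives to negatives, so this arithmetic leaves them alone.

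It is also fair to say that the 90% and 95% inputs are deliberately conservative. At the earlier study's average accuracy the SHCH difference falls from 26.0 to 15.5 points, which is still large.

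Section 8.4 is a summary, and the statistical analysis plan, which is not at hand, could add adjusted values. That would not remove the formulas fixed in Table 7.

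**Conclusion.** The point holds for OST, SHCH and the pooled data. There, the raw-count PPV and NPV in primary endpoint 1.1 estimate a consequence of the enrolment targets. For 95% down to 90% accuracy, SHCH PPV is 26 to 28 points too high, OST NPV 7 to 13 points too low, and pooled PPV 11 to 17 points too high. At the earlier study's average the SHCH PPV excess is about 15 points.

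These sizes assume that the Table 5 targets are met and that exclusions under the composite reference leave the mix unchanged (400/1,400 is also 28.6%). They also take the stated prevalences as the anti-HCV prevalence among eligible attenders. That last assumption is loose. The prevalences are approximate, and the text does not say whether they refer to antibody or to viraemia. For Georgia the two differ (7.7% and 5.4% in section 1.2). Section 3.4.2 also excludes anyone with a history of HCV treatment.

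Kappa is a minor part of the point. This should be fixed, but it does not threaten the study's main accuracy results.

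**What to change.** In section 8.4.1, replace the raw-count PPV and NPV for OST, SHCH and the pooled data. Use values derived by Bayes' rule from the estimated sensitivity and specificity, tabulated over a range of anti-HCV prevalences. The range should include the protocol's 5% and 40% and could add the 2.3% and 7.7% of section 1.2. At 95%/95%, for example, the PPV column would read 30.9%, 50.0%, 61.3% and 92.7% at 2.3%, 5%, 7.7% and 40%.

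For these values, replace the Wilson intervals with intervals that carry the uncertainty in both estimates: delta method on the logit scale, or bootstrap. Do not present pooled raw-count predictive values as field performance. Report kappa with the sample prevalence beside it.

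The cost is one paragraph in the protocol, matching text in the analysis plan and a few lines of code, with no change to recruitment or data. The drawbacks are that PPV will look less favourable and that each value is conditional on an assumed prevalence, which is why a range is better than a single figure.
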